## Intervention

The components and goals of the intervention are outlined in **Table 2.** The main

components are:

- Body weight loss without significant loss of muscle mass, through low energy diet combined with
- Exercise training based on interval training and resistance exercise^20^
- Optimal medical treatment for hypertension and hypercholesterolemia (with statin and ACE-inhibition)
- Risk factor control: smoking cessation aid, nutrition counselling, screening and treatment for diabetes

DEXA scan and exercise capacity measurements are primarily used to ensure and monitor efficiency of exercise and weight loss interventions. The intervention program involves a multidisciplinary approach provided by a team of dieticians, physiotherapists and doctors trained in cardiac rehabilitation. Attention will be given to program flexibility combining structured group-based protocols with individually tailored strategies.

## Table 2. Overview of the components of the 24-week intervention

|  | Target group | Duration | Intervention | sessions | Goal | Responsible |
| --- | --- | --- | --- | --- | --- | --- |
| **Exercise training**  **Week 0-24** | **All** | **1½ h** | **Twice a week** | **Group** | **VO_2_ peak 10% improved** | **Card rehab team: Physiotherapist** |
| **Weight loss**  **Week 0-12** | **All** | **1 h** | **Every second week**  **+**  **1 individual** | **Group**  **+**  **individual** | **10% weight loss** | **Card rehab team: Dietician** |
| **Weight maintenance**  **Week 12-24** | **All** | **1 h** | **Monthly**  **+**  **1 individual** | **Group**  **+**  **individual** | **Heart healthy diet** | **Card rehab team: Dietician** |
| **Smoking cessation** | **Smokers**  **33%** |  | **Pharmacological support** | **Group** | **Quit smoking** | **MUNICIPAL** |
| **Optimized medication** | **LDL > 2**  **SBT >130**  **HbA1c >6.0^*^** | **½ h** | **Statin**  **ACE blocker**  **Metformin** | **Individual** | **LDL < 2**  **BP 130/80**  **HbA1c < 6.5** | **Clinical assistant, MD** |

^*^ Newly diagnosed DM2

##

## Figure 4. Participants’ study plan

## Figure 5. Antihypertensive treatment algorithm

### Exercise training (ET)

ET consists of group sessions of aerobic interval training and resistance exercise, scheduled twice weekly throughout the 24-week intervention period. Each group consists of 10 participants and each session lasts for 1 h. The group sessions are supervised and monitored by a physiotherapist experienced in cardiac rehabilitation. The intensity of the training will be individually adapted to the concomitant weight loss program with restricted calorie intake. During the first 12 weeks of calorie restriction, the training will be modest in load and intensity and primarily consist of short aerobic interval sessions and resistance exercise of the large muscle groups.

Attendance at training sessions will be registered by the physiotherapist. Home based training is accepted, if participants cannot attend all the sessions. Compliance of home-based training is self-reported (registered by a telephone call to the participant). Lack of compliance is defined as < 50% attendance to training sessions/home training. Lack of compliance within the first five weeks of intervention will lead to withdrawal from the study and possibly new inclusion.

**Please see Figure 6** for an overview of the estimated timeline of the training sessions throughout the study period. The 30 participants in the intervention group attend at 3 teams of 10 participants.

## Figure 6. Overview of exercise training group sessions

[figure not shown]

### Low energy diet (LED)

Weight loss will be achieved by following an evidence-based LED formula delivered by Cambridge Weight Plan. The diet, consisting of shakes, soups and bars, allows the participant to consume 800-1200 kcal/day. The diet contains the daily need of energy as well as macro- and micronutrients, proteins, essential fatty acids and recommended daily doses of vitamins and minerals^29^. The goal of the intervention is a total weight loss of at least 10% without significant loss of muscle mass.

Participants will be offered comprehensive support to fulfill the weight loss through a combination of two individual meetings and group sessions with a dietician. Attendance in a group session (5-7 participants and a dietician) defines the beginning of the 24-week interventional period for each participant. The purpose of this meeting is information about the LED treatment. Hereafter, participants are offered a single individual meeting with the dietician in order to register weight and dispense the Cambridge Weight Plan diet. Participants then follow a 12-week period with LED and attend group sessions every second week with their team and a dietician. The purpose of the group sessions is to motivate, adjust treatment to individual concerns, and monitor weight and compliance to intervention. During the 12^th^ week, participants will be offered another individual meeting with the dietician in order to motivate and advise in the weight maintenance diet.

The recommended weight maintenance diet is high in protein and with a low glycemic index modified from the DiOGenes study.^30^ Taking into consideration that the participants have CMD the high protein diet is adapted to resemble the Mediterranean diet, which is low in saturated fat (< 10%) and recommended to heart patients,^31^ with protein sources mainly from fish, poultry, egg, dairy, and vegetables. During the 12 weeks of weight maintenance the participants will be encouraged to still attend the monthly group sessions with the dietician. In case of weight gain LED can be used to replace meals. No weight loss within the first three weeks of LED is considered as lack of compliance and leads to withdrawal from the study.

The dietary group sessions will be scheduled at baseline (week 0) and week 1, 3, 5, 7, 9, and 11 and last for 60 minutes. In the weight maintenance period from week 12-24 the sessions will be scheduled monthly. The two individual sessions with dietician will scheduled in week 0-2 and optimally in week 12 and last for 60 minutes. Please see **Figure 7** for a schematic overview.

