# Aims

The aim of this study is a ‘proof-of-concept’, i.e. to determine whether a comprehensive

intervention is feasible and results in improvement in both angina and CMD.

The study is a pilot study which we, if successful, will seek to expand to a multicenter interventional trial with prognostic outcome in collaboration with an international

consortium.

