## Randomization

A third party unrelated to the study will perform randomization of participants with randomly permuted block sizes of 2,4, and 6 using the ralloc program in Stata 11. Replacement of participants will be possible in case of dropout.

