# Statistics

## Sample size

The primary endpoint is change in microvascular function assessed by CFVR.

We wish to be able to detect a difference in change in CFVR between groups of 10%, equal to a change in CFVR of 0.24, assuming a baseline mean CFVR of 2.4. According to our previous study (22) the standard deviation of the within individual change is assumed to be 0.3. With power of 0.8 and two-sided significance level of 0.05, 26 patients should be included in each group. With 26 in each patient group we will be able to detect a moderate or larger effect on symptom burden. Anticipating dropout, randomization of a total of 60 patients was chosen. Dropout within the first three weeks of inclusion is replaced by new inclusion.

SAQ has four subscales each with a score from 1-100. We have not found data on within-study subject variation on SAQ. However, previous trials have obtained changes in SAQ of 10-20 points after intervention.^18^ ^46^ ^13^ A trial of 46 patients (predominantly women) with microvascular angina randomized to either ranolazine, ivabradine or placebo for four weeks found a SAQ score change of 10-40 points across different SAQ parameters, all highly significant (p<0.001).^18^ We will conduct a study on a similar study population, and we therefore expect to have the statistical power to document clinically relevant effects.

With 60 participants included, the probability is 80 percent that the study will detect a treatment difference at a two-sided 0.05 significance level, if the true difference between treatments is 11. This is based on the assumption that the standard deviation of the response variable is 15.

Analyses will be performed in STATA/IC 13.1. Categorical data will be presented as number (percentage), continuous data as mean (SD) or median (interquartile range) if normal distribution cannot be assumed. Regression analysis will be performed with the primary outcome change in symptoms (SAQ) and the independent variable change in CFVR.

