# Costs

## Table 3. Overview of estimated costs of the 24-week intervention

| **24-week intervention** | **Item in intervention** | **Time (hours)** | **Salary/hour** | **Costs (DKK)** |
| --- | --- | --- | --- | --- |
| ET group sessions (physio) | 3h/week x 24 weeks x 3 teams of 8 participants | 216 | 200 | 43.200 |
| VO_2_max test (CPET) baseline + follow-up (physio) | 45 min/participant x 130* | 97½ | 200 | 19.500 |
| LED group sessions (dietician) | 1 h x 6 teams x 9 times | 54 | 254 | 13.716 |
| Weight registration e.g.  (dietician) | ½ h x 54 times | 27 | 254 | 6.858 |
| Weight loss individual sessions (dietician) | 1 h/participant x 70* times | 70 | 254 | 17.780 |
| Cambridge Weight Plan Diet | 3 meals daily x 12 weeks x 70 participants* | 0 | Sponsored | 0 |
| Smoking cessation group sessions (nurse) | 3 sessions x 1 h  (10 participants) | 0 | Municipal | 0 |
| **Total costs, all patients** |  |  |  | **101.054** |

*10 participants extra in case of drop-out and new inclusion. CPET includes control group participants.*

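### Women who do not comply with diet or training are withdrawn from the study after randomisation under rules that no control can meet, with no week-24 follow-up planned, so the comparison can be biased towards the intervention

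*Protocol*

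**What the plan says.** Women are randomised 1:1 after baseline, and the intervention starts afterwards (Protocol, Study design and Blinding). Two compliance rules then apply:

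- **Diet** (Low energy diet (LED)): "No weight loss within the first three weeks of LED is considered as lack of compliance and leads to withdrawal from the study".
- **Training** (Exercise training (ET)): non-compliance means attendance below 50%, with home training counted. The consequence is: "Lack of compliance within the first five weeks of intervention will lead to withdrawal from the study and possibly new inclusion".

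Withdrawal criteria also lists poor compliance with diet, training or medicine and refers to the methods chapter for definitions. That chapter defines the first two but gives no threshold for medicine. Under Controls – usual care, controls receive no diet or training programme, although the study doctor may manage their medication.

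Replacement is described in three places:

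- Randomization gives a general permission: "Replacement of participants will be possible in case of dropout".
- The training rule above says that new inclusion is possible.
- Sample size is definite, for either arm: "Dropout within the first three weeks of inclusion is replaced by new inclusion".

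The footnote to Table 3 budgets for "10 participants extra in case of drop-out and new inclusion". The aim is to determine whether a comprehensive "intervention is feasible and results in improvement in both angina and CMD".

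**The concern.** Both defined rules act after randomisation and can remove women from one arm only. If a withdrawn woman is not measured at week 24, the comparison is between early compliers in the intervention arm and all controls. Women who comply early may differ in prognosis from those who do not, and randomisation no longer balances that difference. This affects the primary endpoint, CFVR, as well as SAQ, VO2peak and weight. Weight is affected most directly, because the diet rule filters one arm on an early value of a listed secondary endpoint.

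Feasibility is also at stake. The women for whom the programme failed early are the ones withdrawn. If others take their places and the first women are not counted, the programme looks more feasible than it was.

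This is not a matter that can wait for an SAP. An SAP can define analysis sets, but it cannot supply a week-24 CFVR that was never measured.

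**Working it through.** **1. Who can be removed.** The diet and training rules need a diet and a training programme, which only the intervention arm has. The schedule of assessments has week 0 and week 24 only, and the text states no follow-up after withdrawal. The flowchart and study-plan figures could not be read. Table 3 costs 130 exercise tests, which would fit 70 at baseline and 60 at follow-up, that is, no follow-up test for 10 replaced women. Other splits are possible, so this is consistent with the reading but does not prove it.

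**2. The plan's own figure.** Sample size takes a difference "equal to a change in CFVR of 0.24, assuming a baseline mean CFVR of 2.4", and states that "the standard deviation of the within individual change is assumed to be 0.3".

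n per group = 2 × (1.96 + 0.842)² × 0.3² / 0.24² = 24.5, rounded up to 25. With the t distribution it is 25.5, rounded up to 26, which is the stated figure. The arithmetic is sound; the question is who is counted.

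**3. Selection with no true effect.** Assume that a share p of the intervention arm, the least compliant, is removed, and that compliance correlates ρ with CFVR change (normal model). Neither p nor ρ is in the protocol. SD is kept at 0.3 with 30 analysed per arm.

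- Shift = ρ × 0.3 × φ(z_p) / (1 − p)
- SE = 0.3 × √(2/30) = 0.0775
- Type I error = 1 − Φ(1.96 − shift/SE) + Φ(−1.96 − shift/SE)

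| p | ρ | φ(z_p)/(1 − p) | Shift | Shift/SE | Two-sided type I error |
|---|---|---|---|---|---|
| 10% | 0.3 | 0.1755/0.90 = 0.195 | 0.018 | 0.23 | 5.6% |
| 25% | 0.3 | 0.3178/0.75 = 0.424 | 0.038 | 0.49 | 7.8% |
| 25% | 0.5 | 0.424 | 0.064 | 0.82 | 13.0% |

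A second form sets the gap between retained and removed women at g standard deviations, so that the shift is p × g × 0.3. It gives 5.1% (p = 10%, g = 0.25; shift 0.0075) to 16.2% (p = 25%, g = 1; shift 0.075).

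**4. Selection with a true effect.** Assume 0.24 in compliers and no gain in removed women. The effect as randomised is 0.24 × (1 − p). Power is Φ(effect/0.0775 − 1.96) at 30 per arm.

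| p | Effect as randomised | 0.24 / effect | Power, 30 per arm | n per arm for 80% power |
|---|---|---|---|---|
| 10% | 0.216 | 1.11 | 0.80 | 31 |
| 20% | 0.192 | 1.25 | 0.70 | 39 |
| 25% | 0.180 | 1.33 | 0.64 | 44 |

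The 25% row supposes that all 10 budgeted extras replace intervention women: 10 of 40 = 25%.

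**5. Feasibility.** In that same case 40 women start to fill 30 places. Retention is 30/40 = 75%, but a report on the final 30 would show 30/30.

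**6. Replacement passages.** One passage has no time limit. One counts five weeks from the start of intervention and one counts three weeks from inclusion. Methods accepts up to four weeks between baseline and the start of intervention, so three weeks of diet can end 4 + 3 = 7 weeks after baseline. Whether a woman withdrawn under the diet rule is then replaced depends on which passage is followed. The text also does not say whether a replacement takes over the vacated allocation or is randomised afresh.

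**The case against.** Several stronger readings are tempting, and the documents do not support them.

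- **That every removed woman is replaced, and only in the intervention arm.** The diet rule mentions withdrawal only, the training rule makes new inclusion a possibility, and the one definite replacement rule covers dropout in either arm. The undefined medicine criterion could in principle reach a control. Only the diet and training triggers are one-sided.
- **That the replacement windows flatly contradict each other.** They concern partly different events on different clocks. The fault is unclear scope.
- **That the dropout allowance makes replacement unnecessary.** Moving from 52 to 60 allows 4 of 30 per arm (13%). At 25% removal, 30 × 0.75 = 22.5 remain, below the required 26.
- **That the effect will be overstated by a third.** The 10 extras are not split by arm. Table 3 also budgets diet products for 70 participants although 30 women are planned for the intervention arm, so it is a weak guide. No gain at all in removed women is an extreme assumption, because the intervention also includes medication. The contrast of 0.24 with 0.18 is partly a difference between two target quantities, the effect in compliers and the effect as randomised, and not bias alone.
- **That the feasibility result is lost.** Attendance is registered and weight is monitored, so withdrawals can be counted against all randomised women. Nothing forbids it.

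Follow-up CFVR is also read blind. In addition, the protocol reports an RC of 0.70 for repeat CFVR in an overweight population. If RC means 1.96 times the SD of a difference, that SD is 0.70/1.96 = 0.36, already above the assumed 0.3. Variation that is mostly measurement noise cannot correlate strongly with compliance, which favours the lower end of the range in step 3.

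These points limit the size of the effect and the wording of the concern. They do not touch the core: one arm is filtered after randomisation, and no week-24 data are planned for the women removed. Blinded reading cannot correct for who is missing.

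**Conclusion.** The point holds in this form: following the protocol as written can bias the arm comparison towards the intervention, and can overstate feasibility if withdrawn women are replaced and not counted. The direction is the expected one, but the size cannot be fixed from the protocol. Under the correlation model it runs from almost nothing (a shift of 0.018) to about a quarter of the planned difference (0.064/0.24 = 27%). The overstatement of 1.33 is the upper end of the scenarios shown and needs both of its assumptions: all extras in the intervention arm, and no gain in those removed.

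It should be corrected before women are withdrawn under these rules, because missed week-24 assessments cannot be recovered at analysis.

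**What to change.** 1. In Withdrawal criteria, Exercise training (ET) and Low energy diet (LED), replace withdrawal from the study for non-compliance with wording that separates any stopping of treatment from leaving the study. Whether treatment is stopped is a clinical decision on which this point takes no position.
2. Invite every randomised woman who still consents to the week-24 assessment, and analyse her in her allocated arm.
3. Report the three-week weight criterion and the 50% attendance criterion as feasibility results, with all randomised women as denominator. Otherwise use them only in a supportive per-protocol analysis.
4. Reconcile Randomization, Exercise training (ET) and Sample size on replacement. Any further women should enter by fresh 1:1 randomisation, and no woman already randomised should be removed from the analysis.

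The cost is protocol wording, a few more week-24 visits and a possibly smaller reported effect. The protocol should state the power from step 4. At 10% non-compliers who gain nothing, 30 per arm still gives about 80%. At 20% or 25% it does not, and the sponsor would have to accept the lower power or randomise more women.

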## Figure 7. Overview of diet sessions

[figure not shown]

Both ET and dietician sessions will be conducted at Frederiksberg Hospital, Dept. of Cardiology.

### Controls – usual care

Usual care for patients with no CAD disease is normally provided by the patient’s general practitioner and does not comprise intensive lifestyle intervention or medical treatment. If controls in this study need medical therapy for hypertension or hypercholesterolemia, this will be effectuated by the researcher, MD. Then, controls will be monitored with blood pressure and LDL blood samples and receive medicine adjustments according to National Prevention Guidelines (NBV) during the full study period.

### **Echocardiography – strain**

Diastolic heart function tends to be impaired in obesity and in diabetes^33^ but whether this is also the case in microvessel dysfunction is unclear.

Improvement in cardiac function following intervention may be subtle and is more likely measurable during stress. By using global longitudinal and radial 2D strain at rest and during dipyridamole or adenosine stress, we expect that we will be able to detect a smaller difference in myocardial function than by using change in LVEF assessed by the Simpsons method.

### Exercise capacity (VO_2_ peak)

A cardiopulmonary exercise test (CPET) is performed using a bicycle ergometer (Corival, Lode, Germany) with breath-by-breath gas exchange measurements (Jaeger, Vyntus CPX, Germany. Participants will be encouraged to continue until exhaustion. Criteria for VO_2_peak are levelling off of VO_2_ despite increasing workload and peak respiratory exchange ratio (peak RER) > 1.10.^38^ VO_2_peak and peak RER are determined at peak effort with 15-second average measurements. ^39^ VO_2_peak is expressed as: VO_2_peak (mL/min), VO_2_peak (mL/kg body weight/min) and VCO_2_peak (mL/min).^40^ Predicted VO_2_peak is calculated using the equation for sedentary, overweight individuals presented by Wassermann and Hansen.^39^ Measured VO_2_peak in percent of predicted is determined.

### Dexa scan and body composition

The loss of lean body mass should be considered when planning a weight loss protocol since a decrease in lean body mass has been linked to increased mortality.^41^ ^42^ To estimate body composition (body fat mass and fat free mass ) a whole body dual X-ray absorptiometry (DEXA) scan will be performed.

Body composition, body weight, hip and waist circumference will be measured in the morning after a 10-hour fast. Waist circumference is measured halfway between the lower rib and the iliac crest and hip circumference at the maximal gluteal protuberance and calculated as an average of two consecutive measurements.

### Clinical examination

Blood pressure, heart rate, weight.

### Questionnaires:

In research settings the Seattle Angina Questionnaire and Hospital Anxiety and Depression Scale are the most commonly used, validated questionnaires for assessing angina symptom burden and anxiety and depression, respectively.

### Seattle Angina Questionnaire - SAQ

Improving quality of life is one of the primary goals in treating patients with stable angina pectoris. Quality of life is increasingly used as a patient-centered endpoint in cardiovascular disease studies, especially for stable ischemic heart disease. From a patient point of view angina may be the most important factor reducing quality of life, and data suggest that angina frequency predicts higher rates of cardiovascular events and death.^43^ Angina symptoms may not always be associated with an impaired CFVR, and conversely^44^ but interventions with ACE-I^18^ or weight loss ^45^ have improved angina symptoms (assessed by SAQ or Canadian Cardiovascular Society, CSS) and CFVR in previous studies.

The SAQ is a reliable, predictive tool that has been validated in 175 women with a confirmed diagnosis of stable coronary artery disease (CAD) and angina pectoris ^46^. It is a 19-item health-related quality-of-life measure for patients with coronary artery disease. The answers given by the patients in the SAQ’s questions are used to calculate scores in five scales:

- Anginal Stability: Whether a patient’s symptoms are changing over time.
- Anginal Frequency: Present frequency of symptoms.
- Physical Limitation: How much a patient’s condition is hampering her physical abilities.
- Treatment Satisfaction: How well a patient understands and what she thinks of it.
- Quality of Life: A measure of the overall impact of a patient’s condition on her interpersonal relationships and state of mind.

Scale scores are transformed to a 0-100 range by subtracting the lowest possible scale score, dividing by the range of the scale and multiplying by 100. Higher scores indicate less symptom burden. Because each scale monitors a unique dimension of coronary artery disease, no summary score is generated. A score change of 10 points is clinically perceptible to patients and is considered a clinically relevant difference, while a substantial change is considered to be a change of 20 points^47^ (please see Appendix for SAQ).

